### Randomization and study groups

Randomization will occur at the level of the PHC supervisor. This is being done to avoid contamination of intervention effects into control clinics since each supervisor routinely supports multiple clinics. Each PHC clinic supervisor will be randomly assigned in a 1:1 ratio to the intervention or control arm. The study investigators would provide a list of facilities and supervisors to be randomized using a computer-generated randomization list generated by study statistician. In South Africa, a PHC clinic supervisor fulfills a management role at PHC clinics [42], and are mandated to ensure smooth clinic operations through oversight of clinic performance against set targets including patient clinical outcomes and programme performance targets, and oversees the implementation of clinical guidelines. Each PHC clinic supervisor may oversee between three and five PHC clinics within one district. Therefore, through randomization of 14–16 PHC clinic supervisors working in both the Ugu district and King Cetshwayo district, 40 clinics (20 in each arm) will be enrolled into this study as each supervisor oversees on average three to five medium-sized clinics. Not all clinics under the purview of the PHC clinic supervisors randomized will be enrolled into the study. Clinics will be excluded if ART services are not offered on site, services are run by a single nurse, and if they are mobile clinics or clinics located within hospitals. All eligible clinics enrolled in the control arm of this trial will receive the prevailing standard-of-care for TB-HIV integration (Fig. 2) in accordance with the DoH guidelines. While the study team will not interfere with any additional benefit that control clinics may receive (for example, support from other NGOs), changes to the background standard of care will be recorded systematically and accounted for in the final analysis.

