### Statistical analysis

The primary outcome of mortality and secondary outcomes will be analyzed using cluster-summary methods. The primary outcome will be analyzed among TB-HIV co-infected patients only while the secondary outcomes will be analyzed among TB-HIV co-infected, HIV-only, and TB-only patients. Mortality rate per arm will be calculated as geometric mean of cluster-level summaries and will be compared using unpaired *t* test. The same technique will be applied to secondary outcomes. The *t* test applied in cluster-level summaries is one of the robust methods of analyzing unmatched trials especially when there are small number of clusters per arm [50]. Since we have 16 clusters and 40 sub-clusters, multi-level regression will be used as secondary analyses. Proportional hazard regression with random effects (frailty models) will be used for analyses of time-to-event outcomes. Generalized estimating equations and mixed effects linear models will be used for binary and quantitative outcomes, respectively. These models will take the clustering by PHC supervisor and clinic into account through the random effects. They will also allow us to adjust for baseline variables, especially those with imbalance between arms, as this is likely when clusters are fewer. The HCW interviews will be summarized using descriptive statistics such as means and frequencies. Adjusted baseline descriptive statistics will be calculated as the means of the cluster-level summaries and characteristics of the two arms will be compared using *t* test or rank sum tests. Individual-level summaries at baseline will be compared using *t* test or rank sum tests and Fisher’s exact test. Data will be analyzed with SAS version 9.4 (or higher) (SAS Institute INC., Cary N.C, USA).

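### The individual-level baseline tests ignore the randomisation of supervisors, so their p-values are too small, and the adjusted secondary models choose covariates by observed imbalance

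*Protocol article*

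**What the plan says.** The unit of allocation is the supervisor. The section Randomization and study groups states: "Each PHC clinic supervisor will be randomly assigned in a 1:1 ratio to the intervention or control arm". The Statistical analysis section counts them: "Since we have 16 clusters and 40 sub-clusters".

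That section then plans two separate baseline comparisons:

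- At cluster level: "Adjusted baseline descriptive statistics will be calculated as the means of the cluster-level summaries and characteristics of the two arms will be compared using" t or rank-sum tests.
- At patient level: "Individual-level summaries at baseline will be compared using" the t "test or rank sum tests and Fisher’s exact test". No adjustment for clustering is stated.

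On covariates in the regression models, the section says: "They will also allow us to adjust for baseline variables, especially those with imbalance between arms, as this is likely when clusters are fewer". These models are not the main analysis: "multi-level regression will be used as secondary analyses". The main analysis is set out first: "The primary outcome of mortality and secondary outcomes will be analyzed using cluster-summary methods". No covariate adjustment is stated for it.

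**The concern.** The t, rank-sum and Fisher's exact tests, in their usual form, treat every patient as an independent unit. Here patients arrive in 16 randomised groups, and patients under one supervisor tend to resemble each other. A test that ignores this understates the variance of the difference between arms, so ordinary chance differences between a few clusters come out as significant. This is at odds with the section's own reasoning, which chooses cluster-level t tests for the outcomes because clusters are few.

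Two things are at stake. First, a baseline table with many small p-values casts doubt on an allocation that may be perfectly sound. Second, observed imbalance is the only criterion given for choosing covariates in the adjusted models. That makes the adjusted estimates depend on the data whichever baseline comparison is used to judge imbalance, and imbalance says nothing about whether a variable predicts death. If the patient-level p-values were used for the purpose, the choice would also rest on an invalid test.

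**Working it through.** The article gives no figure for the behaviour of the baseline tests, so there is nothing of its own to reproduce. The question is how often a patient-level test with nominal size 5% rejects when randomisation is sound.

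**Inputs**

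- 16 clusters, allocated 1:1, so 8 per arm (Statistical analysis; Randomization and study groups).
- m = 350 patients per cluster (Sample size estimation). The forecast of 6000 patients over 16 clusters gives 6000/16 = 375.
- Coefficient of variation k = 0.25 to 0.35 and control-arm proportion 15% (Sample size estimation).
- Assumption: a binary baseline variable clusters as mortality is assumed to. The article gives no ICC or k for any baseline variable.
- Assumption: the baseline sample per cluster is about the size of the 12-month forecast. The baseline data are in fact the preceding 12 months.
- Assumption: two-sided testing.

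**Formulas**

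- ICC = k² × p / (1 − p)
- Design effect DE = 1 + (m − 1) × ICC
- Actual rejection rate = 2 × [1 − Φ(1.96 / √DE)]

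**Results with clustering borrowed from mortality**

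| p | m | k | ICC | DE | Rejection rate |
|---|---|---|---|---|---|
| 0.1275 | 350 | 0.25 | 0.0091 | 4.19 | 34% |
| 0.1275 | 350 | 0.35 | 0.0179 | 7.25 | 47% |
| 0.1275 | 375 | 0.35 | 0.0179 | 7.70 | 48% |
| 0.15 | 350 | 0.25 | 0.0110 | 4.85 | 37% |
| 0.15 | 350 | 0.35 | 0.0216 | 8.54 | 50% |

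The value 0.1275 is the midpoint of 15% and 10.5% (15% less a 30% reduction). The value 0.15 is the control-arm figure, which suits a pre-randomisation variable better. Example for the fourth row: ICC = 0.0625 × 0.15/0.85 = 0.0110; DE = 1 + 349 × 0.01103 = 4.85; 1.96/√4.85 = 0.89; two-sided tail 37%.

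**Results over an assumed ICC range (m = 350)**

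| ICC | DE | Rejection rate |
|---|---|---|
| 0.001 | 1.35 | 9% |
| 0.005 | 2.75 | 24% |
| 0.01 | 4.49 | 36% |
| 0.02 | 7.98 | 49% |
| 0.05 | 18.45 | 65% |

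**Check by simulation.** 3000 trials were generated with 8 against 8 clusters of 350, mean prevalence 15% and no systematic difference between arms. Fisher's exact test on pooled patients rejected 37% of the time at k = 0.25 and 49% at k = 0.35. The cluster-level t test on the same data rejected 5.5% and 4.9%. With no clustering, Fisher's test rejected 4.5%, so the excess comes from clustering alone.

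**Expected count.** With ten independent variables clustered in this way, 10 × 0.34 = 3.4 to 10 × 0.50 = 5.0 would be declared significant, against 10 × 0.05 = 0.5 for a valid test.

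The sums take equal cluster sizes. The article expects unequal ones, which would raise the design effect.

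**The case against.** A reader might infer that the patient-level tests select the covariates, so that spurious imbalances will drive the adjusted results. The text does not say so. The adjustment sentence comes before the baseline comparisons, a sentence on staff interviews stands between them, and nothing ties imbalance to a p-value or to the patient-level tests. The valid cluster-level comparison comes immediately before the faulty one, and imbalance could equally be read from that.

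A reader might also infer that the main result is at risk. It is not: the primary comparison is a cluster-summary t test with no stated adjustment, and the regression models are secondary.

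Three further points stand:

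- The differences between arms would be real chance differences, which the article itself expects with few clusters. It is their p-values that are wrong, and adjusting for a chance difference in a prognostic variable is legitimate.
- Giving emphasis to imbalanced variables does not exclude prognostic ones.
- With 16 clusters there are 16 − 2 = 14 between-cluster degrees of freedom, but patient-level covariates do not each use one; only cluster-level covariates do.

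The size of the effect rests on borrowed clustering, so the wider 9% to 65% range should be read beside 34% to 50%. A full covariate list may sit in an analysis plan that is not shown, and its absence from a condensed article is no fault. None of this rescues the patient-level tests, which are stated and do not match the unit of randomisation, or the stated criterion of observed imbalance.

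**Conclusion.** The concern holds in limited form. The article states a baseline analysis whose p-values would be too small. The actual size of a nominal 5% test is about 34% to 50% if baseline variables cluster as mortality is assumed to, and 9% to 65% over assumed ICCs of 0.001 to 0.05, so it exceeds 5% throughout the range examined. The article also names observed imbalance as the emphasis for covariate choice in the secondary models, which is a data-dependent criterion. The two faults may combine, but the article does not say that they do. The consequences fall on the reading of the baseline table and on the secondary adjusted estimates, not on the primary test of mortality.

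**What to change.** In the Statistical analysis section:

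1. Delete the individual-level significance tests at baseline, or replace them with versions that account for clustering by supervisor. Keep the planned cluster-level summaries, and report individual-level descriptives by arm without p-values.
2. For the secondary multi-level models, replace the imbalance criterion with a short list of covariates fixed in advance on prognostic grounds. Baseline cluster mortality from the 12-month retrospective data is a natural candidate. It needs its own definition for that period, since Table 2 counts deaths from clinic enrolment onward. Keep the cluster-level covariates few, because each uses one of the 14 between-cluster degrees of freedom. If the analysis plan already holds such a list, refer to it.

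The cost is wording. There are fewer tests to run, the retrospective collection is already scheduled, and the primary analysis does not change. The Trial status section reports that data are still being collected, so the change can be made before analysis.

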## Discussion

Findings from this trial are expected to provide information on a scalable strategy (a “change package”) to address shortcomings in the implementation of integrated TB-HIV treatment and services. If successful, the strategy could make a contribution to reducing TB-HIV-associated mortality and morbidity in South Africa and other regions of the world where co-infection with TB and HIV is a concern. In 2013, WHO performed a joint review of HIV, TB, and prevention of mother to child transmission (PMTCT) programmes in South Africa, which recommended the need for context-specific mechanisms for the delivery of integrated TB-HIV services at PHC and community level, with particular focus on improving access to TB and HIV services for children, adolescents, and key populations. Some studies undertaken in the South African PHC clinic setting have shown that the QI strategy can be effective as an intervention for PMTCT care [51–54]. To date, there have been no studies that have explored the use of the QI model as an intervention to improve integration of TB and HIV treatment. An important component of the QI model is the PDSA cycle, comprising learning cycles to test and revise theory-based predictions as recommended by Taylor et al. (2014) in their systematic review on the application of the PDSA method to improve quality in healthcare [55]. We anticipate that the findings from this trial will offer an affordable and sustainable strategy through use of the QI model to effectively improve the integration of TB-HIV programmes. The study results will be communicated to stakeholders through dissemination meetings, conferences, and publication in peer-reviewed journals. Recommendations would be made based on the study findings for appropriate actions to be considered and taken by the department of health and relevant authorities in areas with high burden of TB and HIV.

### Trial status

Data collection is currently on-going.

## Abbreviations

ART: Antiretroviral therapy
BREC: Biomedical research ethics committee
CAPRISA: Centre for the AIDS programme of research in South Africa
COACH: Context assessment for community health
CPT: Cotrimoxazole preventive therapy
DHIS: District Health Information System
DoH: Department of Health
GEE: Generalized estimation equations
HBC: High burden countries
HCT: HIV counseling and testing
HCWs: Healthcare workers
HIV: Human immunodeficiency virus
IPT: Isoniazid preventive therapy
PDSA: Plan-Do-Study-Act
PHC: Primary health care
PMTCT: Prevention of mother to child transmission
QI: Quality improvement
SA: South Africa
SUTHI: Addressing challenges in scaling up TB and HIV treatment integration in public health settings in South Africa
TB: Tuberculosis
TIER.Net: Three interlinked electronic register for tuberculosis and human immunodeficiency virus
WHO: World Health Organization
